### Secondary clinical outcomes

Depressive symptoms will be measured using the Urdu-validated Patient Health Questionnaire-9 (PHQ-9) [37], while anxiety symptoms will be assessed using the Urdu-validated Generalized Anxiety Disorder-7 (GAD-7) [38] administered at baseline, 3 months, and 6 months.

Perceived social support will be assessed using the Multidimensional Scale of Perceived Social Support (MSPSS) [39]. Suicide-related cognitions will be measured using the Maternal Suicide Risk Inventory (MSRI) [40], a locally developed 16-item measure capturing inductively derived cognitive pathways to maternal suicidality. These two measures will be administered at baseline, 3 months, and 6 months.

### Implementation outcomes

Adoption, reach, fidelity, feasibility, acceptability, and appropriateness will be assessed using a combination of quantitative indicators (e.g., participation, completion, number of KPZ sessions delivered) and validated implementation scales (AIM, IAM, FIM), alongside qualitative interviews, focus group discussions, and longitudinal reflections with peer mothers, supervisors, LHWs, and medical officers. To understand how well the KPZ intervention was received, a combination of quantitative tools and qualitative methods will be used to explore its relevance, appropriateness, and overall acceptability from the perspectives of those implementing and engaging with it.

Three brief standardized scales, the Feasibility of Intervention Measure (FIM), Acceptability of Intervention Measure (AIM), and Intervention Appropriateness Measure (IAM), will be used to assess how implementing agents perceived the intervention [41]. Each scale contains four items rated on a 5-point Likert scale (from “completely disagree” to “completely agree”). FIM will measure how practical and easy the intervention was to deliver. AIM will assess whether the implementers found the intervention appealing and welcomed the approach. IAM will assess how well the intervention seemed to fit the context and needs of the population. Together, these tools provide a quick yet meaningful snapshot of implementers’ views on the intervention’s usability and relevance.

Finally, peer mother knowledge, attitudes, and confidence to implement KPZ will be assessed using the 30-item Knowledge, Attitudes, and Confidence (KAC) scale (Table 3) [42].

**Table 3 Tab3:** A priori progression criteria for a definitive full-scale trial

	Go-proceed with RCT	Amend-proceed with changes	Stop-do not proceed unless
1.Feasibility of participant recruitment Can 50 trial participants (Assuming each village cluster can recruit 8 participants) be recruited to take part in the study?	If at least 38 trial participants Could be recruited to take part in the study	If < 38 participants are recruited To take part in the study	If < 20 participants are recruited To take part in the study
2. Feasibility of data completion Can at least 70% of recruited participants be retained in the study until completion?	If 70% of recruited participants Are retained in the study until completion of trial	If 70–60% of recruited Participants are retained in the study until completion of trial	If less than 60% of recruited Participants are retained in the study until completion of trial
3.Feasibility of treatment adherence Can t least 70% of participants complete all the 12 sessions of KPZ intervention?	If 70% of recruited participants complete all the 12 sessions of KPZ intervention	If 50–70% of recruited Participants complete all the 12 sessions of KPZ intervention	If less than 50% of recruited Participants complete all the 12 sessions of KPZ intervention

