### Study design

The study is a mixed-methods pilot hybrid type-II stratified cluster randomized controlled trial (cRCT), with six Village Clusters (VCs) allocated in a 1:1 ratio either to the intervention or EUC arm across two UCs (Shah Allah Ditta and Sihala). All study elements were designed alongside a Community Advisory Board (CAB) comprising five women with lived experience of suicidal thoughts or behavior and two LHWs from the study sites. The CAB provided ongoing feedback on all study materials, including recruitment procedures, intervention content, assessment tools, and implementation strategies, ensuring cultural relevance, acceptability, and feasibility. The CAB initially met quarterly during the co-design phase and then annually throughout the study to guide research operations. Recruitment of women of reproductive age is planned to span 1.5 years, with endline follow-ups of all participants 6 months post-recruitment beginning in May 2024.

Mixed-methods include quantitative measures and multiple qualitative methods, including longitudinal periodic reflections, in-depth interviews, focus group discussions, and systematic meeting debriefs to assess implementation outcomes and mechanisms. Longitudinal periodic reflections involve recurring discussions with implementing agents, namely peer mothers, to capture their evolving experiences, challenges, and adaptations over the course of intervention delivery. In-depth interviews with trial mothers, peer mothers, and health system clinicians elicit detailed insights into the feasibility, acceptability, and perceived mechanisms of change, as well as familial, social, and political factors influencing engagement and implementation. Systematic meeting debriefs provide documentation of emerging issues, solutions, and contextual factors that may affect implementation fidelity, reach, and sustainability of the intervention. Together, these qualitative methods allow for a comprehensive understanding of both participant and implementer experiences, inform iterative improvements, and contextualize quantitative outcome measures within the lived realities of the study setting.

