#### Sampling procedures

The trial aims to recruit a total of 50 participants at risk of suicide and allocated into two equal groups: an intervention arm (*n* = 25) and an EUC arm (*n* = 25) based on their cluster randomization. This sample size is consistent with recommended guidelines for pilot randomized-controlled trials [30] and is sufficient for the primary goal of estimating key feasibility parameters, including recruitment rates, retention, and preliminary effect sizes, to inform the design of a future definitive trial, rather than for testing statistical significance. Participants will be identified by screening for suicidal ideation (in partnership with the local government health system) across six VCs. Based on extant literature and preliminary formative data, which estimate a 5–8% prevalence rate, we will screen approximately 800 women to ensure adequate recruitment across this range. The target analytic sample for all subsequent 3- and 6-month follow-up assessments will remain 50 participants, with robust retention strategies employed to minimize attrition. We will also aim to recruit 12 peer mothers to be trained as delivery agents for the KPZ intervention.

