## Intervention discontinuation and participant discontinuation criteria intervention will be discontinued if trial participants develop psychosis or another severe mental disorder.

### Loss to follow-up

Any participant who cannot be followed up at the designated time points (i.e., 3 and 6 months postnatal) will be considered lost to follow up and not contactable by the research team. Those who wish to withdraw consent from further intervention sessions; it will be recorded, and they will be asked if they wish to be followed-up or not, which will also be recorded. In case of consent withdrawal at any follow up, data collected up to that point of withdrawal will be included in the analyses.

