## Measures

Table 1 below summarizes all primary and secondary outcome measures and Table 2 below summarizes all implementation outcome measures, including their descriptions and assessment time points.

**Table 2 Tab2:** Implementation outcome measures

Implementation outcomes		
Outcome measure	Measure description	Time frame
Trial feasibility		
Percent eligible participants who consent	Proportion of individuals who met eligibility criteria and provided informed consent to participate in the study	At recruitment
Percent of consented participants who started intervention	Proportion of participants who initiated at least one KPZ intervention session after consenting	6 months
Percent of participants who completed KPZ safety card	Proportion of enrolled participants who completed the KPZ safety card component	6 months
Percent of participants who completed one brief contact follow up session	Proportion of enrolled participants who completed at least one brief follow-up contact session	6 months
Percent of participants who dropped out of KPZ intervention	Proportion of participants who discontinued participation prior to completing the intervention	3 months and 6 months
Fidelity		
Median number of sessions completed	Median number of sessions completed by participants	6 months
Feasibility		
Feasibility of Implementation Measure (FIM)	FIM is a 4-item feasibility scale [41]. The scale was culturally adapted to fit the study and Urdu language	6 months post-enrollment
Acceptability		
Acceptability of Implementation Measure (AIM)	AIM is a 4-item Acceptability scale to assess perspectives on implementation [41]. The scale was culturally adapted to fit the study and Urdu language	6 months post-enrollment
Appropriateness		
Intervention Appropriateness Measure (IAM)	IAM is a 4-item appropriateness scale [41]. The scale was culturally adapted to fit the study and Urdu language	6 months post-enrollment
Cross cutting across FIM/AIM/IAM		
Individual qualitative interviews with intervention mothers	We will conduct qualitative interviews with trial participants to explore their perspectives on the intervention’s content and delivery, aiming to elicit insights into its feasibility, acceptability, and perceived mechanisms of change.”	Baseline and 6 months post-enrolment

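### Table 3's adherence criterion counts KPZ completers against all recruited women, half of whom get no KPZ, so as printed Go cannot be reached with equal arms

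*Protocol article*

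**What the plan says.** **Sample and arms.** Under Sampling procedures the trial will recruit "a total of 50 participants at risk of suicide and allocated into two equal groups", 25 for the intervention and 25 for EUC. Study design describes a trial "with six Village Clusters (VCs) allocated in a 1:1 ratio either to the intervention or EUC arm across two UCs". The sections on the two arms give the 12 peer-delivered sessions to the intervention arm only; control women receive EUC.

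**Adherence rule (Table 3, row 3).** The Go band is "If 70% of recruited participants complete all the 12 sessions of KPZ intervention". Amend is 50–70% and Stop is below 50%, both again of recruited participants. The retention row directly above uses the same term for the whole trial. Row 3's own question speaks only of participants and names no arm.

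**Recruitment rule (Table 3, row 1).** Go is at least 38. Amend is "If < 38 participants are recruited To take part in the study". Stop is "If < 20 participants are recruited To take part in the study".

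**Related text.** Table 2 defines the safety-card item as "Proportion of enrolled participants who completed the KPZ safety card component", and its brief-contact item also uses enrolled participants. The loss-to-follow-up definition begins "Any participant who cannot be followed up at the designated time points (i.e., 3 and 6 months postnatal". The Recruitment and Follow-up assessments sections time the same visits from recruitment.

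**The concern.** Table 3 is the only progression rule shown, and the trial's stated purpose is to inform a definitive trial. In row 3 the numerator can come only from the KPZ arm, while the printed denominator takes in both arms. A rule built that way measures the allocation ratio as much as adherence. Applied literally, it would return Stop for a programme that nearly every allocated woman completed.

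The likely response is that everyone knows what was meant. The difficulty is that the article supports more than one alternative denominator, and the choice between them can change the verdict. A progression rule is set in advance so that this choice is not made once the counts are known, and the article reports the trial as ongoing.

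**Working it through.** **Inputs.** N = 50 planned, 25 per arm (Sampling procedures); six clusters, 1:1 (Study design); KPZ sessions in the intervention arm only (KPZ intervention arm; EUC arm); adherence cut-offs 70% and 50%, recruitment cut-offs 38 and 20 (Table 3). The cut-offs have no stated derivation. The one figure that can be rebuilt is the recruitment target: 6 clusters × 8 women = 48 against 50, which is close enough to need no comment.

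**Step 1: ceiling as printed.** Maximum score = women in the KPZ arm ÷ all recruited.

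| Recruited, equal arms | KPZ women | Completers needed for Go (70% of recruited, rounded up) | Maximum score |
|---|---|---|---|
| 50 | 25 | 35 | 50% |
| 48 | 24 | 34 | 50% |
| 38 | 19 | 27 | 50% |

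Go needs more completers than there are women who can receive the sessions, at every size with equal arms.

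**Step 2: verdicts as printed, N = 50.**
- 25 of 25 complete: 25/50 = 50%, bottom edge of Amend.
- 24 of 25 complete (96% of the arm): 24/50 = 48%, Stop.
- 70% completion in the arm: 0.70 × 25 / 50 = 35%, Stop.
- If each woman completes with probability 0.90, independently, the chance of avoiding Stop is 0.90^25 ≈ 0.07.

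**Step 3: how unequal the arms would have to be.** Go requires KPZ women ÷ all recruited ≥ 0.70, even with full completion. At N = 50 that is at least 35 in KPZ and at most 15 in EUC, against a plan of 25 and 25.

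**Step 4: the candidate denominators.** The adherence objective (Objectives of the study) refers to women receiving the KPZ sessions. Quantitative analysis applies intention to treat to feasibility analyses, which points to women allocated to KPZ. Table 3 says recruited. With assumed counts of 25 allocated, 22 starting and 16 completing all sessions:
- recruited: 16/50 = 32%, Stop
- allocated to KPZ: 16/25 = 64%, Amend
- receiving KPZ: 16/22 = 73%, Go

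**Step 5: KPZ arm as denominator, cut-offs unchanged.** 0.70 × 25 = 17.5, so Go is ≥18/25 (72%; 17/25 = 68% falls short). 0.50 × 25 = 12.5, so Amend is 13–17 and Stop is ≤12. With X ~ Binomial(25, p), P(X ≥ 18) is about 0.51 at p = 0.70 and 0.89 at p = 0.80, assuming independent women and ignoring clustering. The rule then responds to adherence.

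**Step 6: recruitment bands.** Every count below 20 is also below 38, so the whole of Stop lies inside Amend.

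**Step 7: follow-up anchor.** Women may enter while pregnant or with a child under 3 years. For a woman whose child is already older than 6 months, both postnatal time points passed before enrolment, so that definition cannot be applied to her. It contradicts the post-recruitment timing in Recruitment and Follow-up assessments.

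**The case against.** The strongest reply is that the intended population can be recovered. The adherence objective concerns women receiving KPZ, only the intervention arm gets the sessions, and row 3's question does not use the word recruited. On that reading this is a slip of wording, and an unreachable Go describes a calculation that nobody would run. The first part stands: the KPZ arm was probably meant. It does not cure the rule, because all three bands print the wrong denominator and the text that might correct them points to two different ones (Step 4).

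For recruitment, the columns run in order of severity, so a sensible reader would let Stop govern below 20. That makes the overlap an editorial fault, though a real one.

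Several stronger readings are tempting, and the document does not support them:
- **Exactly 70% is both Go and Amend.** The questions in rows 2 and 3 ask for at least 70%, which settles the tie as Go. With 25 women, exactly 70% cannot occur.
- **The retention bands rest on the postnatal anchor.** No band in Table 3 cites it; row 2 measures retention to the end of the trial. The contradiction lies in the loss-to-follow-up definition alone.
- **The Table 2 items distort a decision.** They carry no thresholds, and feasibility endpoints are summarised descriptively. Aligning them is a matter of consistency.
- **Retention should be met in each arm.** Pooled retention is a legitimate pilot criterion and nothing contradicts it. A per-arm rule would also be much stricter: with independent women and true retention of 80%, the chance of Go falls from about 0.97 (≥35/50) to about 0.79 (≥18/25 in both arms).
- **Retention needs a BSSI-based definition or a rule for a missed 3-month visit.** These are operational details that an article may leave to the full protocol.

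**Conclusion.** The point holds as an error in a printed decision rule. With the planned equal arms, the adherence score cannot exceed 50% against a Go mark of 70%. A single non-completer among 25 yields Stop, and 70% completion in the KPZ arm is scored as 35%. This rests on the literal wording of the bands and on roughly equal arms; cluster recruitment could be uneven, but Go would need at least 70% of all recruits in KPZ clusters. The probabilities in the working also assume independent women, but the ceiling does not depend on them.

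A reader might infer that the trial is bound to fail its own adherence test. The document does not support that, since its adherence objective points to KPZ women. The fault is that the rule as printed does not work and leaves its denominator to be chosen later. The missing floor in the recruitment Amend band and the postnatal wording are smaller, separate errors.

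**What to change.** 1. **Table 3, row 3.** Replace recruited participants with all women enrolled in KPZ village clusters (about 25), whether or not they start sessions, in line with intention to treat. Keep the cut-offs: Go ≥70% (≥18/25), Amend 50% to <70% (13–17/25), Stop <50% (≤12/25).
2. **Table 2.** Use the same denominator for the KPZ safety-card and brief-contact items.
3. **Table 3, row 1.** Write Amend as 20–37, leaving Go at ≥38 and Stop at <20.
4. **Loss to follow-up.** Reconcile the postnatal time points with the 3- and 6-month post-recruitment timing in the Recruitment and Follow-up assessments sections.

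The cost is a few edits to two tables and one sentence. No cut-off, sample size or procedure changes. As the trial is ongoing, the correction should be dated and recorded before completion counts by arm are examined.

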## Qualitative data collection

Qualitative data will be gathered through 8–12 interviews with trial women at risk of suicide; 8–12 interviews with EUC women; and 2 periodic reflections per peer mother. In the intervention arm, trial participants’ interviews will be conducted at two time points, with some interviewed around 1-month post enrollment and others at endline to explore whether there was any change in participant’s view with time/or as the trial progressed. For the EUC arm, women’s interviews will be conducted at endline to explore any facilitators and barriers to receiving referred care, recommendations on what would help suicidal mothers, and experiences with BHU/referral services. For each peer mother, two PR will be completed, one in the first half of implementation and the other in the second half. The qualitative data will explore experiences of the intervention/trial, the course of their suicidality over the 6 months, how the trial/intervention was received/delivered, which aspects worked well or need improvement, and which contextual factors (such as family dynamics, social norms, or health system infrastructure) influenced implementation. Data will be collected in audio recordings (when consented) and detailed field-note summaries that include verbatim quotes. Leveraging template analysis as outlined by [43], findings will be organized into matrices, one for each category of participants, according to the themes that emerged from the data, and the analysis was conducted using these matrices.

### Quantitative analysis

Data will be analyzed using Stata [44] and R [45], following CONSORT guidelines relevant extensions for cluster-randomized and pilot-feasibility trials. Participant flow will be presented using CONSORT diagrams, including numbers screened, eligible, randomized, and analyzed for the primary outcomes. All clinical and feasibility analyses will be conducted based on the intention-to-treat (ITT) principle, where all randomized participants will be included in the analysis in the group to which they were originally assigned, regardless of the treatment they actually received or any protocol deviations. For continuous measures, means (standard deviations) or medians (interquartile ranges) will be reported as appropriate; for categorical outcomes, counts and proportions will be presented.

At baseline, demographic characteristics will be summarized by study arm to assess randomization balance and to facilitate comparison of the distribution of potential confounding factors. For follow-up assessment at 3 and 6 months, clinical outcome measures will likewise be reported by trial arm using summary statistics including means, standard deviations, and interquartile ranges. This consistent reporting structure allows for arm-wise evaluation of outcomes across all time points.

Means and frequencies will be used to describe baseline characteristics, participation rates in the study procedures, instrument/item response rates, and engagement with the peer-mother-delivered intervention. Means and frequencies for each suicide-related outcome (e.g., CSSR-S and BSSI) and secondary outcomes (e.g., PHQ-9, GAD-7) will also be calculated at each assessment point.

Primary and secondary clinical outcomes will be analyzed using mixed-effects models to account for clustering within villages and repeated measures within participants. Continuous outcomes will be analysed using linear mixed-effect models, and binary outcomes using generalized linear mixed-effects models with a logit link, each including fixed effects for study arm, time, and their interaction, and random intercepts for village and participant. Missing data will be handled using these linear mixed-effects models, which account for missingness under the missing at random (MAR) assumption by utilizing all available data points for each participant. Analyses are exploratory and will emphasize effect size estimation and 95% confidence intervals, rather than statistical significance, consistent with the pilot design. To ensure the coverage of confidence intervals is accurate, the Kenward-Roger degrees of freedom correction will be applied to all mixed-effects models. This method specifically corrects both the degrees of freedom and the standard errors to account for the uncertainty in variance component estimation that arises with few clusters, and is expected to produce wider, more conservative confidence intervals. Furthermore, if the model encounters a singular fit due to limited cluster-level information, Bootstrap confidence intervals (percentile method, 1000 iterations) will be utilized as a robust sensitivity analysis, as this does not rely on variance component estimation.

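### Kenward-Roger is not defined for the logit model planned for C-SSRS, and a percentile bootstrap with three villages per arm is not a robust check

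*Protocol article*

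**What the plan says.** All statements on the method are in the protocol article, Quantitative analysis. Continuous outcomes get linear mixed models, and "binary outcomes using generalized linear mixed-effects models with a logit link" are planned for the rest. Both have arm, time and their interaction as fixed effects, and random intercepts for village and participant. The analyses "will emphasize effect size estimation and 95% confidence intervals, rather than statistical significance".

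On small-sample behaviour the section says: "To ensure the coverage of confidence intervals is accurate, the Kenward-Roger degrees of freedom correction will be applied to all mixed-effects models". It then adds a step for a singular fit that arises because the clusters tell the model too little: "Bootstrap confidence intervals (percentile method, 1000 iterations) will be utilized as a robust sensitivity analysis, as this does not rely on variance component estimation". What is resampled is not stated.

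The design is set out elsewhere. Study design describes a trial "with six Village Clusters (VCs) allocated in a 1:1 ratio either to the intervention or EUC arm across two UCs". Sampling procedures plans "an intervention arm (*n* = 25) and an EUC arm (*n* = 25) based on their cluster randomization". Table 3, under Implementation outcomes, works on the basis of "Assuming each village cluster can recruit 8 participants". Table 1 codes C-SSRS as yes or no, so this primary clinical outcome falls under the logit model.

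**The concern.** Accurate interval coverage is the protocol's own stated aim, and intervals rather than tests are its main inferential output. Two of the tools chosen for that aim do not deliver it.

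- **Kenward-Roger.** It adjusts the standard errors and degrees of freedom of a Gaussian linear mixed model fitted by REML. It has no counterpart for a logit mixed model fitted by maximum likelihood. The instruction to use it everywhere therefore cannot be followed for C-SSRS, and nothing takes its place.
- **Bootstrap.** It is offered as a robust check exactly when the data say least about between-village variation. A bootstrap justified by large numbers of clusters has only three per arm to work with. A reader who sees a narrow bootstrap interval next to a wider Kenward-Roger one could take false reassurance from it into the planning of the definitive trial.

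**Working it through.** **Inputs.** Six VCs at 1:1 give 3 per arm (Study design). There are 8 women per VC (Table 3), so 6 × 8 = 48, against a target of 50 (Sampling procedures). The nominal level is 95% (Quantitative analysis). The ICC is not given, because the trial is meant to estimate it (Power calculation); 0 to 0.20 is assumed. The C-SSRS event rate is not given; 5% to 20% is assumed.

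**1. How often is the fit singular?** With one outcome per woman, the village variance is estimated at zero when the between-VC mean square is no larger than the within-VC mean square. The between-VC df are 6 − 2 = 4 and the within-VC df are 6 × 7 = 42, so

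P(singular) = P(F(4,42) ≤ 1/k), with k = 1 + 8·ICC/(1 − ICC).

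| ICC | k | P(singular) |
|---|---|---|
| 0 | 1.00 | 58% |
| 0.02 | 1.16 | 50% |
| 0.05 | 1.42 | 41% |
| 0.10 | 1.89 | 29% |
| 0.20 | 3.00 | 15% |

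Simulation with equal and unequal VC sizes agrees.

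**2. Coverage if villages are resampled within arm.** Resampling 3 villages with replacement reproduces only (3 − 1)/3 = 2/3 of the unbiased variance of an arm mean, and the percentile method uses roughly normal quantiles. The half-width is thus about 1.96 × √(2/3) = 1.60 standard errors, where a t interval on 4 df uses 2.78.

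- Analytic coverage: P(|t4| < 1.60) = 81.5%.
- Enumeration of all 27 × 27 resamples: 80.4%.
- Simulation: 79% to 82% at every ICC from 0 to 0.20, with equal or unequal VC sizes.

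Only 10 distinct resamples exist per arm, so more iterations cannot help.

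The planned contrast is arm by time. I simulated change from baseline to 6 months with a village effect constant over time and an assumed within-woman correlation of 0.5. Village resampling covers 80% to 81%, with or without conditioning on a singular fit. If instead a single post-treatment outcome is compared, coverage after a singular fit falls to about 72%, 67%, 62% and 52% at ICC 0, 0.05, 0.10 and 0.20.

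**3. Other resampling units** (one outcome per woman, over all simulated trials, ICC 0 rising to 0.20):

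| Unit | Coverage |
|---|---|
| Women only | 93–94% falling to 72–76% |
| All six villages, ignoring arm | 82–85%; 3.1% of resamples contain one arm only |
| Villages, then women | 98% falling to 91–92% |
| Parametric from the fitted model | 94–96% falling to 87–89% |
| t interval on VC means, 4 df | 93–96% throughout |

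**4. The rationale.** A bootstrap that refits the mixed model estimates the variance components again in every resample. A parametric bootstrap after a singular fit draws data with a village variance of zero. Neither is free of variance-component estimation.

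**5. Zero events on C-SSRS.** With 25 women per arm and independent events, P(at least one arm has none) = 1 − (1 − (1 − p)^25)².

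| Assumed p | (1 − p)^25 | P(at least one arm has zero events) |
|---|---|---|
| 5% | 0.277 | 48% |
| 10% | 0.072 | 14% |
| 15% | 0.017 | 3% |
| 20% | 0.004 | 0.8% |

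With no events in an arm at follow-up, the arm-by-time log-odds ratio has no finite estimate.

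**The case against.** Several stronger readings are tempting, and the document does not support them.

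- **That the plan's bootstrap covers 80%.** The resampling unit is not named and may be fixed in an analysis plan that is not shown. The 80% belongs to village resampling. Across schemes the range is about 72% to 98%, and two-stage resampling stays close to 95% at low ICC.
- **That the bootstrap replaces the main interval.** It is labelled a sensitivity analysis and added to the mixed model. For continuous outcomes the Kenward-Roger interval remains.
- **That coverage after a singular fit is 50% to 70%.** This needs a post-treatment comparison or village effects that change over time. With balanced data and a constant village effect, the village intercept cancels from the arm-by-time contrast. Village resampling then still covers about 80%, and resampling women does little harm (about 94%).
- **That the rationale is simply false.** A non-parametric percentile interval does not use a model-based standard error, and with balanced data the point estimate does not depend on the variance components. The objection holds for a parametric or refitted bootstrap.
- **That C-SSRS events are rare and the logit model must go.** No event rate is given, women are selected for suicidal ideation, and aborted and interrupted attempts count. Counts and proportions are already planned. A t interval on VC proportions is not a proven substitute: simulated without clustering, it had zero width in 10% of trials at a 5% rate in both arms, and covered 90% at 10% against 5%.

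The 4-df t interval is not perfect either. If used only after a singular fit on a single outcome, it covers about 91%, 88% and 85% at ICC 0.02, 0.05 and 0.10. That is a reason to fix it in advance whatever the fit, and it still does better than village resampling there (70%, 67% and 62%).

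The stakes are modest. The analyses are exploratory, and the progression criteria in Table 3 rest on recruitment, retention and session completion.

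**Conclusion.** The point holds in two parts. First, as written, Kenward-Roger cannot be applied to the C-SSRS model. A linearised pseudo-likelihood version is possible but none is named, so one of the two primary clinical outcomes lacks the stated correction. This rests on the text alone.

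Second, calling the percentile bootstrap robust is wrong with three VCs per arm. Village resampling covers about 80% instead of 95% whatever the ICC between 0 and 0.20. Resampling women under-covers as the ICC rises, provided that the contrast carries between-village variation. The trigger for using it is likely to occur. These figures assume normal outcomes, about 8 women per VC and the ICC range above.

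The consequence is limited to the effect-size intervals that will inform the definitive trial. It does not touch the decision to proceed.

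**What to change.** 1. Restrict Kenward-Roger to the linear mixed models.
2. Replace the percentile bootstrap with a t interval from the six VC-level summaries (change from baseline, or baseline-adjusted means) on 4 df, or 3 df if UC is included. Pre-specify it for continuous outcomes whether or not the fit is singular.
3. Remove the word robust and the rationale about variance components.
4. For C-SSRS, state that Kenward-Roger does not apply, report counts by arm and VC, and name a small-sample method that remains defined when an arm has no events. Keeping or dropping the logit model is the team's choice.

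The cost is a change of wording and a simpler analysis, with no change to data collection. The intervals widen: a 4-df multiplier of 2.78 in place of an effective 1.60 makes them about 1.7 times as wide as those from village resampling, and 3 df (3.18) about twice as wide for the same standard error.
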